# A single-center, open-labeled, randomized, 6-month, parallel-group study to assess the safety and efficacy of allogeneic cultured keratinocyte sheet transplantation for deep second-degree burn wounds: rationale and design of phase I/II clinical trial

**DOI:** 10.1186/s13063-024-08070-4

**Published:** 2024-04-01

**Keywords:** Skin substitute, Burns, Wound closure, Allograft, Keratinocyte

## Abstract

**Background:**

Burn-related injuries are a major global health issue, causing 180,000 deaths per year. Early debridement of necrotic tissue in association with a split-thickness skin graft is usually administered for some of the 2nd- and 3rd-degree injuries. However, this approach can be complicated by factors such as a lack of proper donor sites. Artificial skin substitutes have attracted much attention for burn-related injuries. Keratinocyte sheets are one of the skin substitutes that their safety and efficacy have been reported by previous studies.

**Methods:**

Two consecutive clinical trials were designed, one of them is phase I, a non-randomized, open-label trial with 5 patients, and phase II is a randomized and open-label trial with 35 patients. A total number of 40 patients diagnosed with 2nd-degree burn injury will receive allogenic keratinocyte sheet transplantation. The safety and efficacy of allogeneic skin graft with autograft skin transplantation and conventional treatments, including Vaseline dressing and topical antibiotic, will be compared in different wounds of a single patient in phase II. After the transplantation, patients will be followed up on days 3, 7, 10, 14, 21, and 28. In the 3rd and 6th months after the transplantation scar, a wound closure assessment will be conducted based on the Vancouver Scar Scale and the Patient and Observer Scar Assessment Scale.

**Discussion:**

This study will explain the design and rationale of a cellular-based skin substitute for the first time in Iran. In addition, this work proposes this product being registered as an off-the-shelf product for burn wound management in the country.

**Trial registration:**

Iranian Registry of Clinical Trials (IRCT) IRCT20080728001031N31, 2022-04-23 for phase I and IRCT20080728001031N36, 2024-03-15 for phase II.

## Administrative information

Note: The numbers in curly brackets in this protocol refer to the SPIRIT checklist item numbers. The order of the items has been modified to group similar items (see http://www.equator-network.org/reporting-guidelines/spirit-2013-statement-defining-standard-protocol-items-for-clinical-trials/).

## Introduction

### Background and rationale {6a}

Burn-related injuries are a major global health issue, causing 180,000 deaths per year, and are most commonly observed in low- and middle-income countries [1]. These injuries are not always associated with mortality but also can cause complications including infection, multiorgan failure, and aesthetic outcomes like hypertrophic scars or keloid growth in some non-fatal cases, usually resulting in long-term hospitalization and disability [2]. Burn injuries can cause physical and mental complications for the patients and lead to poor quality of life [3]. In addition, the cost of treating burn injuries is high and increases in association with the percentage of the total injured area [4].

Several etiologies can cause burn-related injuries, such as fire, explosives, electricity, and hazardous chemical substances [5]. Certain occupations dealing with flammable materials, being a smoker, alcohol abusers, and lack of safety in household places are some risk factors that increase the likelihood of burn injuries [6]. According to the global assessment of burn injuries from 1990 to 2019, the age-standardized rates of burn incidence and the mortality rate were decreased, whereas the number of new burn cases had an increasing trend during the last three decades [7].

### Burn injury classification

Classification of burn injuries is crucial for optimal assessment and effective management [8]. Factors related to the severity of a burn injury include the anatomical location of the affected site, the temperature degree, the duration of exposure, and the cause of the injury [9]. Burn injuries can be classified into four degrees based on the progression in different layers of the skin, size, and the depth of the injury [10]. First-degree burns are specified by the involvement of the epidermis layer, which are not emergencies and can be self-limited with proper care within less than a week. In the context of superficial or deep involvement of the dermis, the burn injury is classified as a second-degree injury, associated with scar development in severe cases, and surgical intervention may be needed in some severe cases [11]. Third-degree burn injuries are usually painless, with involvement of the entire skin, and require surgery [12]. In the case of deep tissue damage including muscles and bones, the burn injury is fourth-degree, which usually leads to the loss of the burned limb [13].

### Treatment challenges

Although the skin has the ability to heal itself, severe burns require a range of interventions, such as healing medications, debridement, and skin grafts [14]. Early debridement of necrotic tissue in association with a split-thickness skin graft (STSG), consisting of the epidermis and a small part of the underlying dermis, is usually administered for some 2nd- and 3rd-degree injuries as a standard therapeutic method [15]. However, this approach can be complicated by factors such as lack of proper donor sites, low-quality skin graft, low vascularity, and hematoma formation [16]. In addition, the development of scar tissue and focal contracture can lead to a substantial reduction in joint activity and even loss of function [17].

### Novel therapies

Nowadays, thanks to the advancements in molecular and personalized medicine, the management of burn injuries entered a new era [18]. To date, many progressions have been conducted to ameliorate burn wounds, which facilitates different stages of wound healing including ischemic phase, inflammatory phase, or wound rehydration [19]. Regenerative medicine and stem cell-based treatments have had promising advancements in the management of different types of wounds through accelerating the healing process [20]. The administration of regenerative medicine for burn injuries offered innovative and effective therapies for affected patients [21]. Artificial skin substitutes are developed as advanced medicinal products and have attracted much attention for burn-related injuries [22]. Skin substitutes prevent electrolyte loss, which is one of the major causes of morbidity and mortality in burn injuries. In addition, these skin substitutes have some advantages in comparison with the surgical skin grafts, such as lower infection rate, faster healing process, and less scar tissue [23, 24]. Keratinocyte sheets are one of the skin substitutes that their safety and efficacy have been reported by previous studies [25, 26]. For instance, Kim et al. investigated the effectiveness of the keratinocyte sheet (Kaloderm®) in deep second-degree burn wounds and compared outcomes with standard treatments (chlorhexidine gauze and antibiotic ointment) as control [26].

### Objectives {7}

In phase I of this clinical trial, we are going to design an open-label study to assess the safety and feasibility of the keratinocyte sheet, made by Royan Institute. In phase II of this study, we will assess the safety and efficacy of this product by evaluation of time to wound epithelialization, skin graft take rate, scar assessment, wound closure, and quality of skin structure.

### Trial design {8}

Two consecutive clinical trials were designed, one of them is a phase I, non-randomized, open-label trial, and phase II is a randomized and open-label trial. The second phase will be started after the last follow-up of phase I study, if no SAEs related to the transplantation of keratinocyte sheet is reported. In these studies, we will evaluate the safety and efficacy of allogeneic cultured keratinocyte sheet transplantation for healing deep second-degree burn wounds as well as the superiority of this product to conventional treatments.

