### Outcomes {12}

The primary endpoint for this study is safety, which will be evaluated in all follow-ups by Common Terminology Criteria for Adverse Event (CTCAE), version 5.0 [27]. Furthermore, secondary endpoints of this project are time to wound epithelialization, skin graft take rate, scar assessment, wound closure, and quality of skin structure.

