### Assignment of interventions: allocation

#### Sequence generation {16a}

In phase I of the study, we will enroll eligible patients who meet the inclusion and exclusion criteria. This will be done through an open-label approach. In phase 2, random allocation software will be used as the method for randomization. By means of random allocation, each patient’s wounds will be assigned to one of the three groups: group A (autograft), group B (conventional treatment), or group C (keratinocyte sheet). This allocation will follow a 1:1:1 ratio and will adhere to a computer-generated randomization schedule that considers specific strata based on the wound site. Various wounds within a single patient will be subjected to this analysis. The investigation will involve a comparative analysis of the safety and efficacy of allogeneic skin grafts in contrast to autograft skin transplantation and conventional treatments, which encompass the use of Vaseline dressings and topical antibiotics.

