## Statistical methods

### Statistical methods for primary and secondary outcomes {20a}

After enrollment of all patients, the data will be entered into the SPSS software for statistical analysis. Based on the distribution of data, paired sample *t*-test or non-parametric equal (chi-square test) will be used for comparing the difference in before and after sample data. For comparing each group in phase II, a Student *t*-test or chi-square test will be administered. Moreover, to handle missing data, a multiple imputation test will be used.

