## Discussion

In this study, we explained the design and rationale of a cellular-based skin substitute for the first time in Iran. It has been observed that almost £20,000 per quality-adjusted life year (QALY) is the annual cost of skin graft for 2nd-degree burn injuries [30]. Therefore, designing a substitute for skin grafting can help affected patients and reduces the invasive procedure of autologous skin graft. In addition, conducting this work proposes this product for being registered as an off-the-shelf product for burn wound management in the regulatory bodies of the country.

This project is novel to conduct in Iran; however, some limitations can exist in our work. First, many patients with 2nd-degree burn injuries may experience other trauma or co-existence morbidities, which can make the choice of eligible patients difficult for us. Second, due to its novelty, many patients may not collaborate to participate in this study. Third, many eligible patients may receive other treatment options, prior to transplantation, which can be a confounder for our intervention. We will address possible limitations in our first phase and will try to overcome our limitations in the second phase.

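### Superiority is stated only against conventional treatment; the within-patient autograft comparison has no stated role and gets an unpaired difference test that, if non-significant, cannot support substitution

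*Protocol article*

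**What the plan says.** Trial design {8} sets out the evaluation of safety and efficacy "as well as the superiority of this product to conventional treatments". The Abstract and Sequence generation {16a} describe conventional treatment as Vaseline dressing plus topical antibiotic, and the section on the choice of comparators lists autologous skin transplantation separately. The superiority aim therefore does not extend to autograft.

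Sequence generation {16a} allocates the wounds of each phase II patient 1:1:1 to autograft, conventional treatment or keratinocyte sheet, and announces "a comparative analysis of the safety and efficacy of allogeneic skin grafts in contrast to autograft skin transplantation and conventional treatments".

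Statistical methods {20a} reserves a paired test for before-and-after data. For the arms it says "For comparing each group in phase II, a Student *t*-test or chi-square test will be administered".

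The Discussion gives the motivation: "designing a substitute for skin grafting can help affected patients and reduces the invasive procedure of autologous skin graft". Outcomes {12} makes safety the primary endpoint and places all efficacy endpoints among the secondary ones.

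**The concern.** The two comparators invite different questions. Against Vaseline gauze and topical antibiotic, superiority is the natural aim and is stated. Against autograft, the Discussion's motivation is to spare patients the graft. That is useful only if healing and scar quality do not suffer unacceptably. The protocol does not say whether this comparison is meant as superiority, non-inferiority or description, yet it fixes a test of difference for it.

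Such a test ends in either a significant difference or no significant difference. The second result is compatible with equality and also with a real deficit that a small sample failed to detect, so it gives no support for substitution. The named test also treats wounds from the same patient as if they came from different patients, which discards the main advantage of the design. At stake is what may be concluded about the sheet relative to autograft when phase II is reported.

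**Working it through.** **The plan's own figure.** Sample size {14} gives two-sided α = 5%, power 95%, m = 4, ρ = 0.5, d = 0.45 and the formula n = 2(z_{α/2} + z_β)²σ²{1 + (m − 1)ρ}/(m d²). The variance is not stated; I assume σ² = 0.25, the binary maximum.

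- (1.960 + 1.645)² = 12.99; 1 + 3 × 0.5 = 2.5; m d² = 4 × 0.2025 = 0.81.
- n = 2 × 12.99 × 0.25 × 2.5 / 0.81 = 20.05 per group, or 40.1 for two groups.

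This reproduces the stated 40 as a calculation for one two-group difference of 45 percentage points. The control group is not identified as autograft or conventional. The calculation was not built to exclude a modest loss against autograft.

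**Precision with a paired analysis.** Only the 35 phase II patients are randomized across the three treatments. I assume all 35 give a complete sheet–autograft pair.

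- 95% CI half-width = t(0.975, 34)/√35 = 2.032/5.916 = 0.344 SD of the paired difference.
- True deficit 0.3 SD: noncentrality 0.3 × √35 = 1.775, power 0.41, so the two-sided 5% test is non-significant 59% of the time.
- True deficit 0.4 SD: noncentrality 2.366, power 0.63, so it is non-significant 37% of the time.

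**The unpaired test that the plan names**, treating the wounds as 35 versus 35 independent observations, with deficits in units of the between-wound SD:

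- Deficit 0.3 SD: noncentrality 0.3 × √(35/2) = 1.255, and the test is non-significant 76% of the time.
- Deficit 0.4 SD: noncentrality 1.673, and it is non-significant 62% of the time.

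The two scales differ in general, because the SD of the difference equals the between-wound SD times √(2(1 − ρ)). They coincide at a within-patient correlation of 0.5.

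**Response-rate scale.** The protocol gives no autograft response rate, so the rates are assumptions. The within-patient correlation of 0.5 is also assumed; the protocol uses that value for repeated measures.

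| Autograft vs sheet | Non-significant, unpaired | Non-significant, paired |
|---|---|---|
| 0.90 vs 0.80 | 79% | 63% |
| 0.80 vs 0.70 | 84% | 72% |
| 0.90 vs 0.75 | 62% | 36% |

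**What a margin would ask of 35 pairs.** Assume equal true rates of 0.80 to 0.90, correlation 0.5 and one-sided α of 0.025. Power is Φ(margin/SE − 1.96), with SE = √(2p(1 − p)(1 − 0.5)/35), that is 0.068 at p = 0.80 and 0.051 at p = 0.90. A 10-point margin gives 32% to 50% power, and a 15-point margin gives 60% to 84%.

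**The case against.** A reader might infer that the trial's purpose is to replace autograft. The documents do not support that. Objectives {7} lists safety and feasibility in phase I and then safety and efficacy in phase II ("In phase II of this study, we will assess the safety and efficacy of this product by evaluation of time to wound epithelialization"). For the endpoint, "The primary endpoint for this study is safety". Substitution appears as motivation, in the Discussion and in the background on donor-site limits. Skin substitute is also the name of the product class, so the word alone is not a claim of equivalence.

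A reader might also infer that the investigators plan to treat a null result against autograft as equivalence, or that registration depends on matching autograft. Neither is stated. The registration sentence concerns burn wound management in general. The misreading is a risk left open, not a planned inference.

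The background says that "these skin substitutes have some advantages in comparison with the surgical skin grafts", so a superiority question against grafts is conceivable and a difference test is not incoherent in itself. That stands, but the background and the Discussion then point to different questions, which is a reason to say which one is asked.

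Finally, how a null result is interpreted, and the reporting of a confidence interval, are often left to a statistical analysis plan, and none is shown here. This has weight and limits the point. It does not remove it: the design section states a hypothesis type for one comparator only, and the methods section itself fixes an unpaired test for arms compared within patients. The 0.3 and 0.4 SD deficits come from no endpoint in the protocol and serve only as illustration.

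**Conclusion.** The point holds in a limited form. The protocol states a hypothesis only against conventional treatment and leaves the role of the autograft comparison open. It names a test that ignores the pairing and, if non-significant, gives no support for the substitution rationale. With 35 complete pairs, a paired analysis resolves the difference to ±0.34 SD of the paired difference and misses a 0.3 SD deficit 59% of the time. The unpaired analysis misses a deficit of 0.3 between-wound SD 76% of the time under independence. These figures rest on no missing pairs, two-sided 5% tests and deficits chosen for illustration; lost pairs would make matters worse. The finding concerns a secondary comparison in a trial whose primary endpoint is safety, so it calls for clearer wording rather than a redesign.

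**What to change.** In Trial design {8} and Statistical methods {20a}:

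- Name sheet versus conventional treatment as the superiority comparison.
- Report sheet versus autograft as an estimated within-patient difference with its 95% CI, from a paired analysis.
- State that a non-significant difference will not be interpreted as equivalence or as support for replacing autograft.

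A non-inferiority margin is optional. It is for the investigators to decide, and if they want one it should be fixed before phase II data are seen. It is a real trade-off, since under the rates assumed above 35 pairs would often fail to meet a tight margin even if the treatments were equal.

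The core change needs no extra patients, visits or measurements. Its one small downside is that the claim possible against autograft may be weaker.

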## Methods: participants, interventions, and outcomes

### Study setting {9}

This study will be conducted at Shahid Motahari Hospital, Iran University of Medical Sciences, Tehran, Iran. Shahid Motahari Hospital is one of the burn referral hospitals in Iran. Therefore, the composition of the population referring to this hospital shows the composition of burn patients in the whole country.

### Eligibility criteria {10}

Prior to the commencement of any study procedures, patients are required to sign the written informed consent.

The following are the inclusion criteria:Age between 18 and 70 yearsBoth gendersAcute second-degree burn injuries involving 20–50% of the total body surface area (TBSA)At least one burn injury for phase 1 and three burn injuries for phase 2 with a maximum area of 60 cm^2^ in the trunk or limbs, with intact musculoskeletal tissue

The following are the exclusion criteria:Having underlying diseases which affect wound healing such as cardiovascular disease, diabetes, malnutrition, and hypertensionPregnancy or breastfeedingActive infection, malignancy, or immunosuppressionRespiratory tract injuryHaving additional trauma injury such as fracture or CNS traumaNeed for intensive careUnwillingness to cooperate in the intervention and follow-ups

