#### Intervention description {11a}

In the first phase of the study, following initial resuscitation, patients will receive allogenic transplantation within the first 5–10 days after the injury. After preparing the patient for the surgery and through general anesthesia in the operating room of Shahid Motahari Hospital, Tehran, Iran, debridement of the necrotic tissues will be conducted by the tangential method. After that, an adrenaline-soaked gauze will be placed on the wound site for 3–5 min to control the bleeding. After preparing the underlying condition, a 2nd-degree burn wound with a maximum area of 60 cm^2^ will be selected and will be covered by an allogeneic keratinocyte sheet. In the second phase of this project, the same procedure will be conducted; however, based on the randomization list, three separate wounds of a single patient will be selected, and allogeneic keratinocyte sheet transplantation, autologous skin transplantation, or conventional treatment will be selected for each wound. Encountering any serious adverse events (SAEs), the second transplantation of the keratinocyte sheet will not be administrated and the patient who experienced SAEs will receive conventional treatment. Figure 1 provides a flow diagram for phases I and II of this protocol. In addition, the SPIRIT flowcharts of the study are presented in Figs. 2 and 3.

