#### Concealment mechanism {16b}

The mechanism of implementing the allocation sequence is central randomization. In this study, allocation of participants is performed centrally by a designated system (which generates a randomized list for allocation of patients in different groups) not directly involved in the recruitment or assessment of participants. Central randomization was implemented to ensure unbiased allocation of participants to treatment groups.

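### Phase II study wounds have a size cap but no within-patient size comparability or area adjustment, which can cost precision (not validity) in time to epithelialization

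*Protocol article*

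**What the plan says.** All references are to the Protocol article.

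- **Eligibility criteria {10}** sets the wound rule: "At least one burn injury for phase 1 and three burn injuries for phase 2 with a maximum area of 60 cm^2^ in the trunk" (limb wounds also qualify, and muscle and bone must be undamaged). The burn must be second-degree and cover 20-50% of body surface. There is an upper area limit and no lower one.
- **Intervention description {11a}** says that "three separate wounds of a single patient will be selected", one for each treatment. It does not ask that they be alike in size.
- **Sequence generation {16a}** allocates 1:1:1 within the patient, so that "each patient’s wounds will be assigned to one of the three groups", using a "computer-generated randomization schedule that considers specific strata based on the wound site". Size is not a stratum.
- **Concealment mechanism {16b}**: "The mechanism of implementing the allocation sequence is central randomization".
- **Outcomes {12}** makes safety primary. The "secondary endpoints of this project are time to wound epithelialization, skin graft take rate, scar assessment, wound closure, and quality of skin structure".
- **Statistical methods {20a}** compares the phase II groups by Student t-test or chi-square test and names no baseline wound area term.

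**The concern.** Comparing three wounds in one patient controls for everything the wounds share: age, nutrition, total burn extent and care. It does not control for features of the individual wound. Starting area is an obvious one, because a larger wound may take longer to close under the same treatment. As written, one patient could contribute wounds of 10, 30 and 60 cm².

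Two things are then at stake for time to epithelialization. The within-patient difference carries size noise that could have been avoided, and with 35 patients a chance size imbalance between treatments can partly mimic or mask an effect. The other endpoints are not examined here.

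**Working it through.** **The plan's own figure.** Sample size {14} gives n = 2(z_α/2 + z_β)²σ²{1+(m−1)ρ}/(m d²), with m = 4, ρ = 0.5, 5% type I error, 95% power and d = 0.45. The variance is not stated. With σ² = 0.25 (the largest binary variance) and two-sided α, n = 20.05 per group, or 40.1 in total, which agrees with the stated 40 if that means two groups of 20. The calculation concerns a response rate and uses no wound area or healing time. This point therefore neither depends on that figure nor changes it.

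**Inputs for the precision check.**
- From the article: the 60 cm² cap, 35 phase II patients, three wounds per patient.
- Assumed, because the article gives none of them: areas uniform on 10-60 cm²; closure from the edge, so time is proportional to wound radius and hence to √area; mean closure 21 days (14 as an alternative); other wound-level SD 4 days; a paired contrast.

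**Step 1: spread of √A.** For A uniform on 10-60:
- E(√A) = (2/3)(60^1.5 − 10^1.5)/50 = 5.775.
- Var(√A) = 35 − 5.775² = 1.65, so the SD is 1.284.
- CV = 1.284/5.775 = 0.222.

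**Step 2: SD of closure time from size alone.** 21 × 0.222 = 4.7 days per wound; 14 × 0.222 = 3.1 days.

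**Step 3: standard error of a 35-pair contrast.** SE = √{2(4² + s²)/35}, where s is the size SD. With s = 0 this is √(32/35) = 0.96 days.

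| Mean closure | Influence of size | s (days) | SE (days) | Widening |
|---|---|---|---|---|
| 21 d | full | 4.7 | 1.47 | 54% |
| 21 d | half | 2.3 | 1.11 | 16% |
| 14 d | full | 3.1 | 1.21 | 27% |
| 14 d | half | 1.6 | 1.03 | 7% |

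**Step 4: bias or noise?** A separate simulation used 35 patients, residual SD 4 days, time proportional to √area, and 21 days at 60 cm² (a slightly different scaling from Step 2).
- With randomized wounds the expected size contribution to the difference is 0, and the paired type I error is 0.049-0.050.
- Power for an assumed 3-day benefit is about 0.86-0.87 with equal sizes, 0.73 with areas of 20-60 cm², and 0.56 with 5-60 cm².
- The chance that size alone moves the mean difference by more than 1 day is 10% (20-60 cm²) to 31% (5-60 cm²).

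**Step 5: when it does not matter.** With areas of 50-60 cm², the SD of the within-patient difference due to size is 0.75 days. Size alone then contributes 0.75/√35 = 0.13 days to the SE. The total SE is √{(32 + 0.75²)/35}, about 0.96 days, under 1% wider than with equal sizes.

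**Step 6: is there room to choose similar sites?** Assume a body surface of 1.8 m² (range 1.5-2.1). Three sites of 60 cm² are 180 cm², or 1.0% of body surface (0.9-1.2%). A 20-50% burn is 3,600-9,000 cm², so the sites take up 2-5% of it.

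**The case against.** **Randomization already deals with size.** This stands. A reader might infer that the endpoint systematically compares wounds with different natural healing times. The article does not support that: wounds are randomized within the patient from a central list, so size is balanced in expectation, and the ordinary standard error covers chance imbalance. Error rates break down (0.99-1.00 in the simulation) only if size drives allocation, for example if the smallest wound always receives the sheet and is compared with the largest. Nothing in the article says that it does.

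**The within-patient gain is intact.** This also stands. Pairing removes between-patient variance whether or not the wounds are of equal size. Size noise arises at the wound level and would be present in a parallel-group design too. To say that it undoes the benefit of the design goes too far.

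**The size of the effect rests on assumptions.** True. Edge closure is the most doubtful one, because a sheet or graft covers the wound and may weaken the dependence on area in two of the three arms. The same argument that makes similar sites easy to find also makes a 10-60 cm² spread less likely: surgeons may already choose sites near the cap.

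**A journal article leaves detail to the full protocol and SAP.** This is partly right. Baseline area may well be recorded, since wounds are photographed for ImageJ at each follow-up and the CRF holds photographic information. But the article does state the size rule, the selection step, the stratification factor and the test, and size comparability or adjustment appears in none of them. The comment is on those stated rules.

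**A matching rule could exclude patients.** Fair. The Discussion already expects difficulty in finding eligible patients, and no particular numerical tolerance can be derived from the article. This argues against an entry criterion, not against a selection instruction or an adjusted analysis.

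**Conclusion.** The point holds as one of efficiency, not validity. The stated rules permit unequal wounds within a patient and neither match nor adjust for area. If closure time depends on starting area, time to epithelialization loses precision and is open to chance size imbalance. Under the assumptions shown, the standard error of a 35-pair contrast is about 7% to 54% wider. It is near zero if sites all lie close to 60 cm² or if covering the wound makes area matter little, and the article does not show which case applies.

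The endpoint is one of five secondary endpoints with no stated order, and safety is primary. No effect on safety or on the stated sample size is claimed. The case for acting is that the remedy is cheap and the possible gain is material.

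**What to change.** 1. **Intervention description {11a}**: add that the three phase II sites are outlined to areas as similar as practicable, each within the existing 60 cm² limit, before the allocation is revealed. Make this a selection instruction and not a new exclusion criterion, so that a patient without three similar sites can still enter.
2. **Plans for assessment {18a}**: record the day-0 ImageJ area of each site.
3. **Statistical methods {20a}**: for time to epithelialization, replace the unadjusted comparison with a within-patient analysis (paired or mixed model) that includes day-0 area as a wound-level covariate.

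The cost is one added baseline measurement per wound, using a method already in the plan, and slightly more analysis work. Where close matching is not possible, the covariate can recover part of the lost precision.
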